### Process evaluation

A mixed-methods process evaluation, using qualitative interviews and self-report measures, will explore the acceptability of the intervention, changes in photoprotection activities and psychosocial mechanisms of change. A brief intervention feedback questionnaire, completed immediately after session 6, will be used to record more proximal perceptions of the main content of intervention. Responses to this questionnaire and the profiling questionnaire (see figure 2) will be used to guide prompts during these interviews and give insight into psychosocial mechanisms of change.

The feedback questionnaire is adapted from one used to assess a fat reduction intervention.^29^ It has five items assessing overall perceptions of the programme and its components, the impact on photoprotection activities and whether psychosocial variables have changed as a result of the intervention. The questions assess the extent to which respondents agree with statements about the intervention (eg, ‘Overall the programme was interesting’ (1=strongly disagree to 5=completely agree)) (see online supplementary file 4).

10.1136/bmjopen-2018-028577.supp4Supplementary data

In-depth qualitative interviews will be conducted by a research nurse and health psychologist who were involved in the design and delivery of the intervention. They will not interview participants to whom they delivered the intervention. Interviews will be based on a topic guide and will explore participants’ views of and experiences with XPAND, including more practical delivery-related aspects, such as the optimal number of sessions, preference for telephone or skype sessions and the value of any further booster sessions. All interviews will be audio-recorded, transcribed and coded using thematic analysis^30 31^ in NVivo V.10.

#### Fidelity assurance

A fidelity assessment will be undertaken to examine the extent to which facilitators delivered the key components of the intervention, specified in the intervention manual, during the face-to-face sessions. Independent researchers will apply a fidelity checklist to audio recordings of all session 1 s and session 6 s, as well as and a random selection of subsequent sessions.

### Evaluation of the cost-utility of XPAND

A decision model will be used to assess the cost-effectiveness of the intervention. Decision models allow outcomes and costs associated with alternative care process to be investigated via simulations. Model structures simplify the care process such that specific aspects can be focused on. Advantages of these models are that they can be adapted to reflect the outcomes and costs that occur in a variety of settings (and therefore aid generalisability); they allow evidence to be generated in a time and cost-efficient way; and they enable interventions to be evaluated that may be precluded using trial methods. The structure of the model to be used here will be developed by the health economists in collaboration with the clinical researchers, and will consist of health states that patients may be in over time. Transition between the states will be informed by literature on the progression of the condition, expert opinion and data collected through the trial. The impact of the intervention on these transitions will be determined through the clinical trial. A health service perspective will be used followed by a societal perspective, which will incorporate broader costs.

Service use will be measured via completion of a Client Service Receipt Inventory (CSRI).^32^ This retrospectively assesses use of primary and secondary healthcare services (including surgical interventions), social care, tests/investigations and aids and adaptations (see online supplementary file 5). The cost of these inputs will be calculated by combining the service use data with appropriate unit cost information. Other impacts of XP include additional financial costs for the patient (eg, sunscreen); and time lost from work/education by patients (eg, to attend appointments, receive treatment, manage symptoms). Costs of these effects will be calculated using average wage rates and information on returns to education. Costs will be combined with quality-adjusted life years (QALYs) derived from the EQ-5D-5L. The estimated cost of the intervention will be based on staff time required to deliver it, plus additional training and materials.

10.1136/bmjopen-2018-028577.supp5Supplementary data

### Trial management

An independent Trial Steering Committee (TSC) attended by the research team, two independent researchers and one patient and public involvement (PPI) panel member will meet every 3 months to provide oversight of the trial. Trial data are collected after each measurement period by a member of the research team not delivering the intervention to that individual. Data are managed and entered by the research team, not the statisticians analysing the data. Adverse events are defined as events that occur during participation in the trial. All will be recorded (death; life threatening; hospitalisation; self-harm; attendance at A&E; distress (intervention group)) and reported to the TSC, who will make a judgement on the link to the trial and recommend modifications or discontinuing trial as appropriate.

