### Study design and flowchart

The XPAND trial is a phase II two-armed parallel group RCT, with a delayed intervention control arm. Participants are randomised to either the intervention group who receive the XPAND intervention in addition to routine care between April and June 2018 or the control group who receive routine care in 2018 and then XPAND between April and June 2019. The delayed intervention control group is included to maximise information collection about the intervention due to the extremely rare nature of XP. For example, achievable sample sizes limit the ability to test between-group differences for the psychosocial outcomes with acceptable power and the delayed intervention group allows for intervention-related changes from baseline testing, which is less robust but still useful.

Patient flow through the study is described in figure 1. The baseline assessment takes place in April 2018 (t0). Post-randomisation assessments take place after completion of the intervention in June to July 2018 (t1), after a booster session in August 2018 (t2) and after a long-term follow-up in December 2018 (t3). All participants use a wrist-worn UVR dosimeter continuously from t0 to t2 and complete daily UVR protection diaries for 21 consecutive days at each assessment time point. At each assessment, participants additionally complete patient-reported outcomes. The t3 follow-up does not involve dosimetry or daily UVR protection diary. In addition, the delayed intervention control arm only completes three further assessments in April 2019 (t4) and June–July 2019 (t5), and December 2019 (t6) with dosimetry and daily UVR protection diary completed for 21 days at t4 and t5.

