### Secondary outcomes

The following outcomes relate to between-group comparisons in 2018 and are recorded on the daily UVR protection diary. UVR-related outcomes also use data from the dosimeter.Average daily UVR D-to-F across 21 consecutive days in August 2018 (t2). This is to investigate the stability of any improvement identified in the primary outcome period (June to July 2018), as it will be 4–6 weeks after the main intervention and follows session 7 (the booster session).Average daily total UVR exposure during each of the 21 day periods (t1, t2) and the average daily time outside across all daylight hours and restricted to 11:00–15:00, when UVR levels are at their highest. These data will be gathered from the dosimeter and the UVR protection diary.Average daily proportion of time outside across daylight hours and between 11:00 and 15:00 with ‘very good’ or ‘excellent’ face photoprotection during each of the 21 day periods (t1, t2). The categorisations relate to the Daily Photoprotection Scale (DPS)^3^ developed for the Phase One n-of-1 study in consultation with the UK XP clinical team. Facial photoprotection activities (excluding sunscreen) are ranked according to their relative level of photoprotection. The following combinations are classed as ‘very good photoprotection’: hat, glasses and scarf/buff; hat, glasses, scarf/buff and hoodie. ‘Excellent photoprotection’ is wearing a face visor, which completely covers the face.Average daily proportion of time outside across daylight hours with sunscreen protection, defined as when sunscreen was applied within the previous 3 hours, during each of the 21 day periods (t1, t2).Average daily number of times sunscreen is applied irrespective of time outside during each of the 21 day periods (t1, t2).Average daily measures of mood, automaticity of photoprotection activities, prioritisation of photoprotection compared with other priorities and level of self-efficacy to manage barriers during the two follow-up periods (t1, t2) will be assessed. The single items have been adapted from ecological momentary assessment questions used in our n-of-1 study^3^ (eg, How much do you agree that UVR protection of your face today was something you did automatically without thinking (0=strongly disagree to 10=strongly agree)) and are included on the UVR protection diary (see online supplementary file 1).

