### Sample size calculations

The target sample size for the study is a total of 24 patients (ie, 12 per group), which was based on the ability to detect an average daily UVR D-to-F difference of 0.10 SED between the groups during the June to July 2018 assessment period. This difference was considered clinically meaningful and potentially achievable due to the personalised nature of the intervention. From our Phase One study of UVR exposure, the average daily UVR D-to-F for people diagnosed with XP was 0.27 SED (SD=0.14), with a within-person correlation of *r*
_ICC_=0.31. Thus, the anticipated difference relates to an effect size of d=0.73, or just over a one-third reduction in average daily UVR D-to-F. Adjusting for the design effect due to the dependence of assessments within individuals, a sample size of 20 patients with 21 daily observations has 80% power to detect a reduction of 0.10 SED in average daily UVR D-to-F at the 5% significance level. Accounting for attrition of 20%, based on our previous research, the target sample size was set at 24.

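### Distress is recorded as an adverse event in the intervention group only, so the steering committee would judge its link to the trial without a concurrent control count

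*Protocol article*

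**What the plan says.** Three statements in the protocol article's Trial management section matter here.

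- The definition has no arm restriction: "Adverse events are defined as events that occur during participation in the trial".
- The list that follows does: "All will be recorded (death; life threatening; hospitalisation; self-harm; attendance at A&E; distress (intervention group". Five categories are open to both arms; the sixth, "distress (intervention group", is limited to one.
- Reports go to the TSC, "who will make a judgement on the link to the trial and recommend modifications or discontinuing trial as appropriate".

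The same section describes a contact that exists for every participant: "Trial data are collected after each measurement period by a member of the research team not delivering the intervention to that individual".

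Under Study design and flowchart, the comparator is a concurrent randomised arm: "the control group who receive routine care in 2018 and then XPAND between April and June 2019". Under Secondary outcomes, both arms report daily mood in the diary: "Average daily measures of mood, automaticity of photoprotection activities, prioritisation of photoprotection compared with other priorities", with self-efficacy alongside. Table 1 schedules SWEMWBS and EQ-5D-5L for both groups at t0, t1, t2 and t3. HADS appears only under Exclusion criteria, as a baseline eligibility check.

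**The concern.** Distress has a background rate in any patient group. When a committee has to decide whether distress is linked to a trial, the concurrent control arm is the natural yardstick, and a randomised trial already has one. The rule as written sets it aside for this category.

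Control patients also carry trial burden in 2018: a dosimeter worn continuously from t0 to t2, three 21-day diary periods, and a wait until April 2019 for XPAND. The Patient and public involvement section shows that diary burden was a live issue for the panel. Distress arising from these procedures fits the adverse event definition but falls outside the list.

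Two things are at stake: the quality of the TSC's judgement on attribution, and the completeness of the harms record for an intervention that, according to the abstract, is meant to enter routine care if it succeeds.

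**Working it through.** The article gives no distress rate and plans no test on distress, so there is no stated figure to reproduce. The main check sets the text side by side; the arithmetic afterwards is illustrative.

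**1. What is recorded for whom in 2018**

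| Item | Intervention | Control | Status in the article |
|---|---|---|---|
| Death, life-threatening event, hospitalisation, self-harm, A&E attendance | yes | yes | adverse event, to TSC |
| Distress | yes | no | adverse event, to TSC |
| Daily mood (diary) | yes | yes | secondary outcome at t1 and t2 |
| SWEMWBS, EQ-5D-5L | t0–t3 | t0–t3 | tertiary outcomes |
| HADS | baseline | baseline | eligibility only |

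The second row is the asymmetry. It sits badly with the arm-neutral definition one sentence earlier, and no other section provides for distress in controls as an adverse event.

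**2. Do the both-arm outcomes fill the gap?** Only in part. They allow a randomised comparison of emotional state, but nothing in the article sends them to the TSC as events. Mood is collected only in the 21-day diary windows and the questionnaires only at assessment points, so neither follows patients through the April to June 2018 delivery sessions.

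**3. Does the 2019 phase fill it?** No. Distress in the delayed group may be recorded once it receives XPAND, but by then there is no parallel untreated arm.

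**4. Illustration of size.** The sample size section states: "The target sample size for the study is a total of 24 patients (ie, 12 per group". Hence n = 12 per arm. The event counts below are assumptions.

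The exact (Clopper-Pearson) 95% interval for x events in n has lower limit Beta(0.025; x, n − x + 1), taken as 0 when x = 0, and upper limit Beta(0.975; x + 1, n − x).

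- x = 0: 0% to 26.5%. The upper limit is 1 − 0.025^(1/12) = 0.265.
- x = 3: 3/12 = 25%, interval 5.5% to 57.2%.

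Under the stated rule, that is all that can be said about distress events. With a control count, Fisher's exact two-sided test would give:

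| XPAND | Control | p |
|---|---|---|
| 3/12 | 0/12 | 2 × C(12,3)/C(24,3) = 440/2024 = 0.22 |
| 3/12 | 3/12 | 1.00 |
| 6/12 | 0/12 | 2 × C(12,6)/C(24,6) = 1848/134596 = 0.014 |

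The same 3/12 reads differently beside 0/12 than beside 3/12, although neither comparison would be decisive. The wide intervals come from the sample size, not from the asymmetry. What the asymmetry removes is the second column.

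**The case against.** The best defence is that the restriction may be deliberate. Control patients have no facilitator sessions in 2018, whereas intervention patients have seven one-to-one sessions, so the category may be a safety trigger for distress seen in that contact. This is plausible, and it is a good reason to keep a session-based line. The article does not state it, however, and it does not explain leaving out distress that control patients might have from the dosimeter, the diary or the wait.

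A second defence is that a journal article condenses adverse event procedures. That would excuse missing detail. It does not excuse an explicit restriction to one arm.

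A third is that 12 per arm is too few for equal recording to settle much. This stands, and it limits the gain from the fix.

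Three stronger readings are tempting, and the document does not support them:

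- *Distress is the harm most likely from XPAND.* It is the only category tied to the intervention group, but the article does not rank harms.
- *Distress in control patients goes uncaptured altogether.* This is true only of adverse event reporting. Mood, SWEMWBS and EQ-5D-5L give an indirect view in both arms, and serious consequences such as self-harm are recorded without restriction.
- *XPAND will show excess distress by construction.* The article plans no between-arm comparison of adverse event rates; the TSC judges events for their link to the trial. A spurious excess would arise only if someone read the unrecorded control count as zero.

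**Conclusion.** The point holds as a defect in harms ascertainment, minor to moderate in size. A definition covering all participants is followed by a list that drops distress for one arm, so no concurrent control count of distress events can exist for 2018. Neither the primary efficacy analysis nor any stated figure is affected.

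The conclusion assumes that the parenthesis means what it says and that staff follow it. The size cannot be put more exactly, because the article gives no expected distress rate and the counts above are illustrations.

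**What to change.** Record distress in both arms with the same definition and the same question, asked at the contacts that already follow each measurement period and made by someone not delivering XPAND to that patient. Let the question cover the time since the previous contact, so that the one after t1 takes in the delivery period. Report these counts to the TSC by arm. Keep distress noted during sessions as a separate, intervention-only line, since control patients have no equivalent opportunity for it to be noticed.

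The article reports that recruitment is complete and that the intervention group received XPAND in 2018, so some of these contacts have probably passed. For those, state in the analysis plan, in the report and to the TSC that the distress counts come from one arm only, are descriptive and cannot be compared between arms.

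The cost is one more question per contact and a few more event reports from the control arm. A question that looks back depends on recall, but equally in both arms.

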### Patient and public involvement

PPI has been integral to every step in the development of this protocol. The PPI panel advised on the study design, particularly related to participant burden of completion of the daily UVR protection diary, which informed the decision to limit the follow-up of the delayed intervention control group to a single period of 21 days (June–July 2019, t5). In addition, the panel reviewed all the XPAND intervention participant-facing materials which helped ensure they were appropriate and acceptable. The PPI panel were not involved in the recruitment process. A summary of research findings will be sent to all participants and published papers will be made available.

## Discussion

To the best of our knowledge, this is the first RCT to test a behaviour change intervention to improve adherence to photoprotection in adults with XP; an ambitious undertaking in a rare disease. It uses a robust methodology, both in the systematic development of the intervention and in the use of a clinically relevant novel measurement approach to estimate dose of UVR reaching the face. The inclusion of a process evaluation will provide insight into the workings of the intervention and the mechanism underlying our trial outcomes, as well as information about the acceptability of XPAND, a key consideration for the implementation of the intervention into routine clinical care. We will also have estimates of the cost-effectiveness of the intervention. Furthermore, over and above the obvious clinical advantages of decreasing the risk of morbidity and mortality associated with skin cancer for the UK XP population, if the intervention is efficacious, it will be generalisable to international populations of adults with XP, significant for other conditions requiring photoprotection (eg, Systemic Lupus Erythematosus) and relevant for healthy populations.

## Ethics and dissemination

This research has been approved. The findings will be published in peer-reviewed journals and presented at national and international scientific conferences.

### Trial status

Recruitment completed. Patient involvement in the study will conclude in December 2019.
